**Figure 1 figure1:**
[figure not shown]
Sequence of the exam versions and time conditions randomized for each participant.

At the beginning of each session, the PI will explain the procedure to the participants. The designated time limits will be informed on the first page of the exams. When the time limit of the exam is reached, participants will be stopped and handed the next exam. Only answers marked on a separate answer sheet will be considered. The time will be tracked on a whiteboard. Participants will be instructed to remain until the end of each exam regardless of finishing before the allocated time to minimize the risk of rushing through the test. Participants will start each exam at the designated beginning time.

### Data Analysis

Analyses will be conducted using SPSS Statistics (IBM Corp) [49]. We will first characterize the sample by group (ADHD vs control), reporting means and SDs for continuous variables and counts and percentages for categorical variables. Between‑group differences in baseline characteristics will be tested using *t* tests (Welch *t* test when variances are unequal) for continuous measures (eg, age and IQ) and chi-square tests (or Fisher exact tests when indicated) for categorical variables (sex, educational level, race, and socioeconomic status). Statistical significance for both data analysis and statistical analysis will be set at a *P* value of .05 or less.

### Sample Size Calculation

For a small to moderate effect size (*d*=0.45), 80 participants are needed to achieve 80% power at a *P* value of .05 or less for within-subject analyses. Participants will be equally divided into 2 groups: clinical group (with ADHD) and control group (without ADHD), with 40 participants in each group.

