### Statistical Analysis

Primary performance analyses will use standardized, IRT‑equated scores from the ENEM‑based exams; raw counts will not be analyzed. Estimated marginal means with 95% CIs will summarize group profiles and within‑person gains. We will also conduct a sensitivity analysis excluding medicated individuals.

Group comparisons at each time limit (40, 50, and 60 minutes) will be performed using Welch *t* tests with Cohen *d* and 95% CIs. Within‑group time effects will be evaluated via repeated‑measure ANOVA with time (40, 50, and 60 minutes) as a within‑subject factor; the Mauchly test will assess sphericity, and Greenhouse-Geisser corrections will be applied when necessary. Planned paired contrasts (50 vs 40 and 60 vs 40 minutes) will use Bonferroni adjustment, and partial η^2^ will index omnibus within‑subject effects.

To directly test whether extended time benefits participants with ADHD more than controls, we will fit a linear mixed‑effects model with a random intercept for participant, coding time continuously in minutes (40, 50, and 60) so slopes are interpretable per minute. Fixed effects will use Satterthwaite df, and interaction tests will be corroborated with likelihood ratio comparisons under maximum likelihood.

Assumptions will be examined using Shapiro-Wilk tests and *Q*-*Q* plots (normality), Levene tests (homogeneity), and visual inspection of mixed‑model residuals. When ANOVA assumptions are not met, inference will prioritize mixed‑model results. Analyses will be conducted in R (*lme4* and *lmerTest*, *emmeans*, and *afex* packages; R Foundation for Statistical Computing).

Missing data will be handled using multiple imputation under the assumption that data are missing at random, and all analyses will be conducted on the imputed datasets using an intention‑to‑treat approach.

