## Results

### Overview

The study was funded in February 2023, and data collection started in August 2023. Data analysis began in March 2026, and no projected timeline for the publication of results is currently available. As of March 2026, a total of 103 participants have been enrolled and allocated to either the control group (n=43, 41.7%) or the ADHD group (n=60, 58.3%) based on diagnosis.

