## Discussion

### Expected Findings

This trial protocol describes a controlled experimental study designed to evaluate whether extended testing time confers a differential benefit to students with ADHD compared to students without ADHD. We hypothesize that extended time will improve overall test performance and that the magnitude of improvement will be superior for the ADHD group. We anticipate that students’ performance will improve significantly more with 50% extra time. Furthermore, we hypothesize that students with ADHD who present greater cognitive and functional deficits will derive greater benefits from extended time accommodations.

In this paper, we propose a study with an experimental design and the development of a standardized task that can be replicated to investigate this issue in college students. The protocol describes a much more robust methodology than those used in prior studies. Lovett and Leja [24] did not include participants with ADHD in their sample. Rather, they examined the association between the effects of extended time and the severity of ADHD symptoms in a nonclinical sample. In addition, the study used only a very short reading comprehension task of 10 minutes, with 5 additional minutes to complete the assignment. Neuropsychological tests were also administered immediately before the session, which may have influenced the participants’ performance. We will administer the neuropsychological assessment on a different day to avoid possible fatigue or carryover effects that could confound test outcomes. Miller et al [23] adopted a similar task to that used by Lovett and Leja [24], also with a short duration (20 minutes). The task developed for our study has a standard time of 40 minutes, with 25% and 50% extra time implemented across 3 parallel versions of the task. In contrast, the previous studies applied the time extension to a single version of the task. This was only possible because we designed the task using the IRT, which allowed us to create psychometrically equivalent parallel versions. Furthermore, the weighted score produced by the IRT provides a more precise estimate of the participants’ abilities. Finally, to the best of our knowledge, our study will be the first of its kind to be conducted in Latin America, which can inform about the effectiveness of extended time in a diverse academic system.

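### The stated 80% power fits one unadjusted within-group contrast; it does not carry over to the Bonferroni-adjusted contrasts, and it does not cover the ADHD-versus-control comparison of gains

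*Protocol article*

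**What the plan says.** The Sample Size Calculation section holds the only power statement. It takes d=0.45 and concludes that "80 participants are needed to achieve 80% power at a" significance level of .05. The statement is limited in scope: it is made "for within-subject analyses". The total is split evenly between the ADHD and control groups, "with 40 participants in each group". The standardiser of d and the sidedness of the test are not given.

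The Statistical Analysis section evaluates time effects within each group and adds a multiplicity rule: "Planned paired contrasts (50 vs 40 and 60 vs 40 minutes) will use Bonferroni adjustment". It gives the between-group question its own test, a linear mixed model with time in minutes and interaction tests.

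The Discussion (Expected Findings) describes the study as designed to "evaluate whether extended testing time confers a differential benefit to students with ADHD compared to students without ADHD". The Results (Overview) report 103 people enrolled, 60 with ADHD and 43 controls.

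**The concern.** A stated power should describe the tests that will be run. Here the calculation is limited to within-subject analyses and uses the unadjusted .05 level, while the plan adjusts its paired contrasts. The question the study is built around is whether the ADHD group gains more than the control group, and no calculation covers it. A between-group difference in gains is estimated much less precisely than a gain within one group, so the 80% cannot be borrowed for it.

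What is at stake is how a non-significant interaction is read. With the 80% figure in the background, it could be taken as showing no ADHD-specific benefit, when the chance of detecting a difference as large as the planning value may have been only moderate.

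**Working it through.** **Inputs from the article.** d=0.45; 80% power; alpha .05; 40 per group planned; two planned paired contrasts with Bonferroni, so alpha .05/2 = .025 each; 60 ADHD and 43 control enrolled.

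**Inputs assumed.** Two-sided tests. First reading of d: SD units of the paired gain. Second reading: SD units of the score, with correlation r between conditions. No effect size is given for the interaction, so 0.45 is carried over to it for illustration.

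**1. Reproduce the stated figure.** Paired t test, noncentrality d√n on n−1 df. At n=40: 0.45 × √40 = 2.846 on 39 df, critical t 2.023, power 79.3% (normal approximation 81.2%). The exact requirement is 41 per group and the normal approximation gives 39, so totals of 78 to 82 bracket the stated 80. All 80 people pooled in one paired test would have 97.8%, so under this reading of d the figure belongs to a contrast within one group.

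**2. Apply the plan's Bonferroni rule.** Same noncentrality, alpha .025; at n=40 the critical t is 2.331.

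| n in the group | Power at alpha .025 |
|---|---|
| 40 (planned) | 69.6% |
| 43 (control, enrolled) | 73.3% |
| 60 (ADHD, enrolled) | 87.9% |

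For 80% at this level, 50 per group would be needed.

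**3. Difference in gains between groups.** With time linear at 40, 50 and 60 minutes, each person's slope is the 60-minus-40 gain divided by 20, so a two-sample t test on gains is a fair stand-in for the mixed-model interaction. Noncentrality is δ/√(1/n₁+1/n₂), with δ in SD units of the gain.

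- 40/40, δ=0.45: 0.45/0.2236 = 2.012 on 78 df, power 51.1%.
- 60/43, δ=0.45: 0.45/0.1998 = 2.252 on 101 df, power 60.7%.
- With mixed-model degrees of freedom: 51.6% and 61.1%.
- 80% at δ=0.45 would need 79 per group.
- If the control gain were half the ADHD gain (δ=0.225): 17% at 40/40 and 20% at 60/43.
- Difference detectable with 80% power: 0.634 SD of the gain at 40/40 and 0.565 SD at 60/43.

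**4. Sensitivity to the unit of d.** If 0.45 is in score SDs, the effect in gain SDs is 0.45/√(2(1−r)). At r=0.5 this equals 0.45, the first reading.

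| r | Gain-SD effect | Bonferroni contrast, n=40 | Interaction, 40/40 | Interaction, 60/43 |
|---|---|---|---|---|
| 0.3 | 0.380 | 53% | 39% | 47% |
| 0.5 | 0.450 | 70% | 51% | 61% |
| 0.6 | 0.503 | 80% | 60% | 70% |
| 0.7 | 0.581 | 91% | 73% | 82% |
| 0.8 | 0.712 | 98% | 88% | 94% |

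On this reading the Bonferroni shortfall disappears from a correlation of about 0.6, and interaction power at 60/43 runs from 47% to 94%.

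**The case against.** The strongest reply is that the article makes no arithmetic error. It restricts its 80% to within-subject analyses, and that figure reproduces. This stands: a reader might infer that the sample size was miscalculated, and the document does not support that. The fault lies in what the calculation covers.

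Four further points also stand.

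- A reader might say that only one reading yields 80%. A second one does: d in score SDs, correlation 0, all 80 people pooled, which gives 80.3%. It is implausible, because it needs one person's exam scores to be uncorrelated, and it leaves 71% under Bonferroni and 29% (40/40) to 35% (60/43) for the interaction. It does not rescue the plan, but it rules out the word "only".
- The 70% belongs to the planned 40 per group. As enrolled, the adjusted ADHD contrast exceeds 80%.
- A reader might take 51% to 61% as the trial's interaction power with its uncertainty. It is neither: the two ends are planned and enrolled numbers under one assumed effect, and the article proposes no interaction effect.
- A reader might see the 60/43 enrolment as a departure from 40/40. It is not a defect: the equal split was the plan, both groups exceed 40, and power rises.

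It can also be said that nothing in the article announces that a null interaction will be read as equal benefit, and that 95% CIs are planned for group profiles and within-person gains. That is correct, so the misreading is a risk and not a stated intention. The article does not, however, explicitly promise an interval for the interaction.

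Finally, a condensed article may leave the standardiser of d to the full protocol. Its absence alone would not be a finding. It matters here because the power of the planned tests cannot be judged without it.

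**Conclusion.** The concern holds as a limit on what the stated power covers. The 80% describes a single unadjusted contrast within one group. Taking d in SD units of the gain and two-sided tests, the planned Bonferroni contrasts have about 70% at 40 per group, and 88% (ADHD) and 73% (control) as enrolled. The comparison that the study exists to make was given no power calculation; this part does not depend on how d is read.

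The size of any interaction shortfall is conditional: about 51% at 40/40 and 61% at 60/43 for an assumed difference of 0.45 SD of the gain, lower for a smaller difference, and 47% to 94% at 60/43 if d is in score SDs with correlation 0.3 to 0.8. The document does not support a flat statement that the trial is underpowered for the interaction.

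**What to change.** Reword the Sample Size Calculation paragraph so that it:

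1. says that the 80% applies to a single unadjusted within-group contrast, and states the unit of d;
2. gives the power under the planned Bonferroni adjustment (about 70% at 40 per group if d is in SD units of the gain);
3. says that the group-by-time interaction was not separately powered, and gives its detectable difference at 80% power (about 0.63 SD of the gain at 40/40 and 0.57 SD at 60/43), labelled as conditional on that unit and, for 60/43, as computed after enrolment.

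In Statistical Analysis, add that the interaction will be reported with its 95% CI, and that a non-significant result will be interpreted from that interval and not as evidence of equal benefit.

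The cost is a reworded paragraph and one added sentence, with a less favourable headline figure. No participants are added and no test changes. Analysis began in March 2026 and no publication date is projected, so the wording can be settled before results appear.

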### Statistical Analysis

Primary performance analyses will use standardized, IRT‑equated scores from the ENEM‑based exams; raw counts will not be analyzed. Estimated marginal means with 95% CIs will summarize group profiles and within‑person gains. We will also conduct a sensitivity analysis excluding medicated individuals.

Group comparisons at each time limit (40, 50, and 60 minutes) will be performed using Welch *t* tests with Cohen *d* and 95% CIs. Within‑group time effects will be evaluated via repeated‑measure ANOVA with time (40, 50, and 60 minutes) as a within‑subject factor; the Mauchly test will assess sphericity, and Greenhouse-Geisser corrections will be applied when necessary. Planned paired contrasts (50 vs 40 and 60 vs 40 minutes) will use Bonferroni adjustment, and partial η^2^ will index omnibus within‑subject effects.

To directly test whether extended time benefits participants with ADHD more than controls, we will fit a linear mixed‑effects model with a random intercept for participant, coding time continuously in minutes (40, 50, and 60) so slopes are interpretable per minute. Fixed effects will use Satterthwaite df, and interaction tests will be corroborated with likelihood ratio comparisons under maximum likelihood.

Assumptions will be examined using Shapiro-Wilk tests and *Q*-*Q* plots (normality), Levene tests (homogeneity), and visual inspection of mixed‑model residuals. When ANOVA assumptions are not met, inference will prioritize mixed‑model results. Analyses will be conducted in R (*lme4* and *lmerTest*, *emmeans*, and *afex* packages; R Foundation for Statistical Computing).

Missing data will be handled using multiple imputation under the assumption that data are missing at random, and all analyses will be conducted on the imputed datasets using an intention‑to‑treat approach.

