Despite its widespread use, the empirical evidence supporting the efficacy and specificity of extended testing time remains limited. While existing findings suggest that extended time can benefit students under time pressure conditions, it is not exclusive to those with ADHD as it also helps students without academic difficulties [17]. This raises important questions about the validity and fairness of such accommodations as specialists argue that valid accommodations must produce significantly greater improvements for the target group compared to those not eligible for the accommodation [18,19].

A systematic review of educational accommodations for children and adolescents with ADHD found 9 studies evaluating the effectiveness of extended time [17], but they exhibited significant methodological limitations that warrant important consideration. First, only 2 of them had experimental designs [20,21]. Second, they were all carried out in the United States and relied on predominantly White samples. Third, most were conducted before 2007, the most recent one having been published 10 years ago [22]. When we look at studies focusing on the college population, we find that they are both scarce and inconsistent, varying in study design [23,24]. Furthermore, again, the existing research has been conducted exclusively in the United States, limiting the generalizability of findings to diverse educational systems and cultural contexts. These methodological gaps highlight the need for more robust research to determine whether extended testing time achieves its intended purpose. Considering the cognitive heterogeneity of individuals with ADHD [25], a variance in response to the accommodation within the clinical group is also possible—which has also not been addressed by previous studies. Another important aspect is determining how much extra time should be provided. Today, this decision is grounded in common sense reasoning.

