Given these gaps, this study aims to assess the impact of additional test time on the performance of college and college-prospective students with and without ADHD. Using an experimental design, we will vary extended time conditions (25% and 50% extra time). We hypothesize that the performance of students of both groups will be superior when additional time is provided but that students with ADHD will potentially experience greater relative benefits. We anticipate that students’ performance will improve significantly more with 50% extra time. Furthermore, we hypothesize that students with ADHD who present greater cognitive and functional deficits will derive greater benefits from extended time accommodations.

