#### Intervention Procedures

To minimize fatigue, the intervention will be administered on a separate day from the psychiatric and neuropsychological assessments in groups of 5 to 15 participants and will always be administered in the morning. To assess participants’ optimal performance, they will be instructed to take medications as usual. Information regarding dose and time of intake will be collected on the day of the intervention. Each session will be facilitated by at least one assistant and the principal investigator (PI). Sessions will be conducted in quiet university or preparatory school classrooms to maintain a naturalistic environment.

Each participant will complete an academic exam with 3 different versions (A, B, and C) of similar difficulty and length. Each version will be paired with 1 of 3 distinct time conditions: 40 minutes (standard), 50 minutes (25% extra time), and 60 minutes (50% extra time). To control for potential confounding variables and ensure that the results are not biased by the order of conditions or exam versions, both the sequence of the exam versions and the time conditions will be randomized for each participant, as illustrated in Figure 1. This counterbalanced design ensures that each participant experiences all 3 time conditions (40, 50, and 60 minutes) and each exam version (A, B, and C) in a different order, preventing any systematic influence from order effects on the outcomes. Sequences of task orders will be computer generated using a random number generator and then counterbalanced so that each condition appears equally often in each position across participants.

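### The dose hypothesis (more improvement with 50% extra time) is most naturally a 60 vs 50 minute comparison, and no planned analysis tests that comparison

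*Protocol article*

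**What the plan says.** The Introduction treats dose as an open question: "Another important aspect is determining how much extra time should be provided". For the design it says "we will vary extended time conditions (25% and 50% extra time", and its hypotheses include "We anticipate that students’ performance will improve significantly more with 50% extra time". The Discussion (Expected Findings) repeats that sentence. Neither place says what the 50% condition is compared with.

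Intervention Procedures defines the conditions as "40 minutes (standard), 50 minutes (25% extra time), and 60 minutes (50% extra time".

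Statistical Analysis then lists these analyses of the exam score:

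- Welch tests of ADHD against control at each time limit.
- Within each group, a repeated-measures "ANOVA with time (40, 50, and 60 minutes) as a within"-subject factor.
- "Planned paired contrasts (50 vs 40 and 60 vs 40 minutes) will use Bonferroni adjustment".
- A random-intercept mixed model for the group comparison of benefit, "coding time continuously in minutes (40, 50, and 60) so slopes are interpretable per minute".
- Estimated marginal means with 95% CIs, as summaries of group profiles and within-person gains.

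The section names no 60 vs 50 contrast, no categorical time term in the mixed model and no test of non-linearity.

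**The concern.** The dose sentence follows a separate hypothesis that extra time helps both groups. If it meant only 50% extra against standard time, it would add little to that hypothesis. Read as 50% against 25%, it needs the difference between 60 and 50 minutes, and both listed contrasts use 40 minutes as the reference.

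This is not detail left to an unseen analysis plan. The article lists its contrasts, and the list does not match its own hypothesis. At stake is one of the questions the trial sets itself, namely how much extra time to give. The planned results could look uniformly positive whether or not the second 10 minutes adds anything.

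**Working it through.** **Inputs.** d=0.45, 80% power, P of .05 or less, 40 per group (Sample Size Calculation); times 40, 50 and 60 minutes (Intervention Procedures); 103 enrolled (Results). Assumptions: two-sided tests, and d taken as the mean within-person difference divided by its SD. The article gives no effect size for 60 vs 50.

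**1. The plan's own figure.** Normal approximation for a paired test: n = ((1.96 + 0.84)/0.45)² ≈ 38.7, so 39. The exact noncentral t gives 41. At n=40 the noncentrality is 0.45 × √40 = 2.85 and power is 79.3%. The stated 80 is therefore reproduced as 2 × 40: one paired test per group at unadjusted .05.

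**2. What each planned analysis tests.**

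| Analysis | Tests 60 vs 50? |
|---|---|
| Welch tests at each time | No; they compare groups, not times |
| Three-level ANOVA | Not specifically; any difference among the three times can trigger it |
| Planned contrasts | No; both are against 40 |
| Mixed model, linear time | Only by assuming equal steps |
| Estimated marginal means | Summary; no 60 vs 50 test named |

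**3. The linear term.** The least-squares slope weights for 40/50/60 are (t − 50)/Σ(t − 50)² = (−10, 0, +10)/200 = (−0.05, 0, +0.05). With complete data the slope is (mean at 60 − mean at 40)/20, and the 50-minute mean drops out.

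| Gains over standard at 40, 50, 60 | Slope per minute | Implied 60−50 gain | True 60−50 gain |
|---|---|---|---|
| 0, 0.45, 0.45 | 0.0225 | 0.225 | 0 |
| 0, 0.225, 0.45 | 0.0225 | 0.225 | 0.225 |
| 0, 0, 0.45 | 0.0225 | 0.225 | 0.45 |

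Three different answers to the dose question give the same slope.

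**4. Plateau truth (0, 0.45, 0.45), by simulation.** n=40, independent normal errors, SD of differences 1, contrasts at .05/2 = .025. The slope is significant in 79% of trials, 50 vs 40 in 70%, 60 vs 40 in 69%, and both contrasts together in about 54%. A direct 60 vs 50 test at .05 rejects in 5%, its nominal error rate.

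**5. Comparing two P values does not help.** Under the linear truth (0, 0.225, 0.45) the two 10-minute steps are equal. At n=40, 60 vs 40 is significant and 50 vs 40 is not in about 51% of trials, the commonest pattern. With all 103 pooled that pattern (49%) is tied with both being significant (50%). The pattern says little about whether the steps differ.

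**6. Power once 60 vs 50 is added.**

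- d=0.45, n=40: 69.6% at .025 (two contrasts) and 63.6% at .05/3 = .0167 (three contrasts).
- If the 60 vs 50 step is half of 0.45, d=0.225. At unadjusted .05, noncentrality is 0.225 × √40 = 1.42 with power 28% at n=40, and 0.225 × √103 = 2.28 with power 62% pooling 103. At .0167 and n=40, power is 15%.
- Range for the 60 vs 50 effect at n=40 and .0167: 15% at d=0.225, 64% at d=0.45.
- Omnibus test at .05, then each pairwise test at .05, within one group of 40, linear truth: 60 vs 40 is found in about 69%, the same as Bonferroni over two, and 60 vs 50 in about 27%.

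**The case against.** The strongest reply is that the comparator is unstated. If 50% extra was meant against standard time, 60 vs 40 tests it and only the wording is loose. This stands as a caveat. The 25% condition and the stated question of how much time to give make the other reading likelier, but a reader should not take it as settled.

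Second, the marginal means could display a 60−50 gain, and a positive slope implies that 60 exceeds 50. Both are true. The first is not a named test and the second assumes the equal steps that are in question.

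Third, a reader might infer that the dose conclusion will rest on one contrast being significant and the other not. The article does not say so; that would be a guess about conduct. The supportable statement is only that no planned analysis tests the difference.

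Fourth, a reader might infer that the trial's main purpose is undermined. It is not. The stated objective is efficacy and specificity, and the extension-against-standard contrasts and the ADHD-by-time interaction remain in place. Dose is one of several claims to novelty, and the data collected allow a 60 vs 50 estimate.

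Fifth, low power for 60 vs 50 might seem to make the contrast pointless. An estimate with its CI still informs the dose question, including when it is imprecise.

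**Conclusion.** The concern holds as a mismatch between a stated hypothesis and a stated list of contrasts. On the natural reading (50% against 25%), no planned analysis tests the dose hypothesis, and the planned tests can all be positive when 60 minutes is no better than 50. The simulated size depends on the assumed plateau at d=0.45, independent normal errors and 40 per group. The slope result needs only complete data.

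Should-fix, not more: the comparator is ambiguous, the other planned inferences are unaffected and the remedy is small.

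**What to change.** State the comparator. If it is 25% extra time, add 60 vs 50 as a named paired contrast, reported with its estimate and 95% CI in each group, and adjust for three contrasts. State that dose will not be inferred from one contrast being significant and the other not. If standard time was meant, reword the sentence in the Introduction and Discussion instead; no new contrast is then needed.

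For the adjustment, Bonferroni over three is simplest and costs about 6 points of per-contrast power at n=40, d=0.45 (70% to 64%). An omnibus-gated closed test within each group avoids that loss, keeping about 69% for 60 vs 40 under a linear pattern, but there it gains nothing for that contrast over the present two-contrast Bonferroni. It controls error within one group only; running it pooled and by group as well would leave error across those families uncontrolled.

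The edit is a few sentences and needs no new data. Because analysis began in March 2026, the change should be dated and should say whether results by time condition had been seen. If they had, the contrast should be labelled post hoc. The report should also acknowledge that power for 60 vs 50 may be low.

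### Holm in place of Bonferroni for the two planned time contrasts would add some power at the same family-wise error rate

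*Protocol article*

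**What the plan says.** Under Statistical Analysis, time effects within each group are tested by repeated-measures ANOVA and followed by two contrasts: "Planned paired contrasts (50 vs 40 and 60 vs 40 minutes) will use Bonferroni adjustment". No step-down, closed or ordered procedure is named. The Data Analysis section sets the level: "Statistical significance for both data analysis and statistical analysis will be set at a *P* value of .05 or less".

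The Sample Size Calculation assumes an effect of the following size: "For a small to moderate effect size (*d*=0.45". It concludes that "80 participants are needed to achieve 80% power at a *P* value of .05 or less for within-subject analyses", "with 40 participants in each group". It makes no allowance for the adjustment. The Results overview gives the enrolled numbers: "control group (n=43, 41.7%) or the ADHD group (n=60, 58.3". It also says that data analysis began in March 2026.

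The Introduction expects that "performance will improve significantly more with 50% extra time", so the 60-minute condition is thought likely to show the larger effect.

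**The concern.** Single-step Bonferroni holds each of the two contrasts at .025, whatever happens to the other. Holm tests the smaller P value at .025 and, if that is rejected, the other at .05. The family-wise error rate stays at or below .05 under any dependence between the tests, and nothing that Bonferroni rejects is lost. When both contrasts have real effects, Bonferroni therefore gives up some power with no gain in error control.

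The loss falls mainly on the weaker contrast. If the Introduction's expectation is right, that is 50 vs 40 minutes, the comparison that shows whether the smaller extension helps.

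**Working it through.** **Inputs.** From the protocol: two contrasts, level .05, d = 0.45, 40 planned per group, 43 and 60 enrolled. Assumed: two-sided tests; d in SD of the paired difference; a family made up of the two contrasts within one group, hence .025 each; and a correlation of 0.5 between the contrasts. They share the 40-minute score, and 0.5 follows from the equal variances and equal correlations implied by the model's "random intercept for participant".

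**1. The plan's own figure.** For a paired t test the noncentrality is d√n = 0.45 × √40 = 2.846.
- Normal approximation at .05: Φ(2.846 − 1.960) = Φ(0.886) = 81.2%.
- Exact noncentral t at .05: 79.3%. The stated 80% with 40 per group is reproduced.
- Exact noncentral t at .025, the level Bonferroni imposes: 69.6%.

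**2. Decision rules.** Bonferroni rejects both contrasts only if both P ≤ .025. Holm rejects both if both P ≤ .05 and the smaller is ≤ .025. Each rejects at least one exactly when the smaller P ≤ .025, so that probability is identical.

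**3. Power by simulation** (pairs of correlated paired t tests, 400,000 simulated trials per case):

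| n | d (50 vs 40 / 60 vs 40) | Quantity | Bonferroni | Holm |
|---|---|---|---|---|
| 40 | 0.45 / 0.45 | each contrast | 69.5% | 75.2% |
| 40 | 0.45 / 0.45 | both | 54.8% | 66.2% |
| 43 | 0.45 / 0.45 | each contrast | 73.2% | 78.7% |
| 43 | 0.45 / 0.45 | both | 59.5% | 70.5% |
| 43 | 0.45 / 0.45 | at least one | 86.9% | 86.9% |
| 60 | 0.45 / 0.45 | each contrast | 87.8% | 91.5% |
| 60 | 0.45 / 0.45 | both | 79.9% | 87.2% |
| 60 | 0.45 / 0.45 | at least one | 95.8% | 95.8% |
| 43 | 0.225 / 0.45 | 50 vs 40 | 20.8% | 28.8% |
| 60 | 0.225 / 0.45 | 50 vs 40 | 29.6% | 39.7% |

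Check: with equal effects, power per contrast is half the sum of the both and at-least-one probabilities. For n = 43 under Holm, (70.5 + 86.9)/2 = 78.7%. The per-contrast gain is therefore half the gain for both.

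**4. Sensitivity to the correlation** (n = 40, both effects 0.45). Power to show both rises from 48.5% to 61.9% at correlation 0, from 60.3% to 70.0% at 0.8, and from 65.0% to 72.3% at 0.95. The gain thus runs from 13.4 down to 7.3 points for both, and from about 7 down to about 4 per contrast.

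**5. Error rate** (n = 40). With no true effect, the family-wise error is the same for both methods: 4.9% at correlation 0, 4.7% at 0.5, 4.1% at 0.8 and 3.3% at 0.95. With one true null and the other effect at 0.45, Holm's error is at most 4.2%.

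**The case against.** **Nothing is invalid.** Bonferroni over two pre-named contrasts is prespecified and protects the error rate. That stands: this is a matter of efficiency.

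**The gain is easily overstated.** A reader might infer that about 11 points of power are lost throughout. At d = 0.45 for both contrasts, that figure is the gain for rejecting both in the smaller group. The gain per contrast is about 5 to 6 points with 43 people and about 4 with 60. A gain near 11 points on one contrast needs the other to be almost certain of rejection.

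**The trial's central question is elsewhere.** A reader might infer that the differential benefit for ADHD, or the whole dose question, depends on this choice. The documents do not support that. Differential benefit is tested by the mixed-model interaction, which is untouched. No section makes success depend on both contrasts. The expectation that 50% extra time helps more is not tested by either contrast, since neither compares 60 with 50 minutes.

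**Bonferroni buys something.** It has simple matching simultaneous intervals and Holm does not. The protocol plans 95% CIs but does not call them simultaneous, so the loss is small, though not nil.

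**A fixed order might look better still.** Testing 60 vs 40 first and then 50 vs 40, each at .05, raises the first contrast from 73% to 82% (n = 43, equal effects). It lowers 50 vs 40 from about 73% to 72%, and to about 29% if 60 vs 40 is the weaker effect (0.225 against 0.45). It can therefore harm the very contrast that needs help.

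**Timing.** Analysis has begun, and a less conservative rule can only add significant results. This stands and governs how the change may be made.

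**Conclusion.** This is a cheap improvement and corrects no error. At the same family-wise error rate and with no extra recruitment, Holm would add about 4 to 6 points of power per contrast and 7 to 11 points for showing both at the enrolled group sizes. It would add about 8 to 10 points for 50 vs 40 minutes if that effect is half the planning value.

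Holm's dominance over Bonferroni is mathematical and needs no trial input. The sizes rest on d being in SD of the paired difference, two-sided tests, a family of two contrasts within each group and a correlation of 0.5. They would differ if the family spanned both groups.

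**What to change.** In Statistical Analysis, name Holm instead of Bonferroni for the 50 vs 40 and 60 vs 40 contrasts, and say that the family is the two contrasts within each group if that is what is meant. Do not add a fixed testing order. Report ordinary 95% CIs beside the Holm-adjusted P values, and say that the intervals are not simultaneous.

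The edit is one word in the plan and one setting in the software. The real cost is procedural: it needs a dated amendment stating that the contrasts had not been seen. If they have been seen, keep Bonferroni as the planned result and show Holm only as a post hoc analysis.
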